### *Outcomes*

#### General Health:

- Changes in Quality of Life: SF-36v2, difference in Physical Component Summary Score and Mental Component Summary Score and 8 domains (T1-T0), (T2-T0)
- Changes in depression score assessed by PHQ-9 questionnaire (T1-T0), (T2-T0)
- Changes in anxiety score assessed by GAD-7 questionnaire (T1-T0), (T2-T0)
- Difference in dietary pattern (reflected by total score) assessed by Mediterranean Diet Score (T1-T0), (T2-T0)

The differences between the randomisation groups on the general health continuous outcomes will follow the same approach as described in section 5 Study objective 1.

[figure not shown]

## **10. Study objective 6**

Utilisation of care in the intervention group is lower than in the control group throughout the study period.

Differences between intervention groups in utilisation of medical care will be tested by linear mixed models with centre as random effect for continuous outcome or mixed models for logistic regression for dichotomous outcomes. When necessary continuous outcome variables will be transformed to obtain a normal distribution.

[figure not shown]

## 11. Study objective 7

To investigate the thesis that the costs of care utilisation in the intervention group are lower than in the control group throughout the study period.

### *Health care cost estimation:*

Direct costs for mobile cardiac rehabilitation will be assigned for the intervention group (with telemonitoring guidance), but not for the control group (no intervention). Care utilization based on activities (clinical admission days, emergency and outpatient clinic visits, GP visits for cardiac (related) complaints or issues, radiology/cardio physiology/nuclear and laboratory tests, and cardiac interventions) will be registered at T1 and T2 and collected by monthly telephone calls with the participants between T1 and T2. A price will be assigned to each service and summed up for each patient individually:

|                                   | Mobile CR | control |
|-----------------------------------|------------------|----------------|
| Costs for CR               | Yes              | No             |
| Costs for care utilization | Yes              | Yes            |

Therefore, total costs (= TC) per patient comprise:

1. Costs for telemonitoring guidance (= CCR, only intervention group)
2. Sum of costs for medical services used outside CR (care utilization, = CCU).

Linear mixed models with centre as random effect will test differences between intervention and control group regarding total costs of care utilisation (see also section 5.1).

Additionally, incremental cost effectiveness ratios (ICER) defined as

$$\frac{\text{Total costs mobile CR} - \text{Total costs control group}}{\text{Outcome mobile CR} - \text{Outcome control group}}$$

will be estimated and a 95% confidence interval will be calculated. Outcome refers especially to the change of peak VO2 and Quality of Life (measured by Physical Component Summary Score and Mental Component Summary Score) during the follow-up period.

[figure not shown]

## 12. Study objective 8

Cardiac patients randomised to the *mCR* programme comply with the use of the smartphone (use of the smartphone on at least 4 days per week with a minimum of 30 minutes of activity per day with a total registration of 150 minutes of activity per week during 21 weeks) during the first 6 months of the study.

Descriptive statistics will be utilised to obtain insight in the use of the smartphone during the first six months of the study. Listed below are the parameters that will be determined.

- Total time (in hours) use of physical activity monitor
- Total time (in hours) use of physical activity monitor with light to moderate intensity
- Total time (in hours) use of physical activity monitor with moderate to high intensity
- Total time (in hours) use of physical activity monitor with high to extreme intensity
- Number of weeks physical activity monitor is used
- Total number of sessions
- Percentage of weeks subject has reached the exercise goal
- Percentage of patients that comply to the exercise goal

Parameters will be summarised in accordance with section 4.6. Summaries will be reported overall and by group.

[figure not shown]

### 13. Study objective 9

One of the main challenges for CR programmes, especially in elderly is to improve participation, adherence and compliance. A significant number of patients refuse or do not follow CR programmes. In this objective the variables (social, psychological, motivational and medical) are identified that could influence participation and adherence. Especially interesting is if new services guide by eHealth solutions (mCR) can improve adherence rates as well as participation rates.

Data from this study is analysed to define the preconditions for sustainable participation, adherence and compliance. Not participating will be defined by screening failure EU-CaRE RCT (see "EU-CaRE and EU-CaRE RCT SAP definitions" document).

The participation rates in all CVD patients that fulfil the inclusion and none of the exclusion criteria, mentioned in section 1.5, and participate in the randomised controlled trial (RCT) are studied. Compliance and adherence, analysing the drop-outs in the RCT is studied. The methodology and statistical methods will be the same used in the other objectives in addition to other suitable approaches related to each specific objective.

For a more homogenous analysis we will study participation in CAD (inclusion criteria 1,2 and 3 of section 1.5) and in each inclusion criteria group.

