#### Secondary study endpoints/outcome

- Difference in  $VO_{2peak}$  from an incremental exercise test (T2-T0, T2-T1)
- Traditional risk factors:
  - Changes in lipid profile (T1-T0, T2-T0, T2-T1)
  - Changes in HbA1C (T1-T0, T2-T0, T2-T1)
  - Changes in renal function (T1-T0, T2-T0, T2-T1)
  - Changes in lean body mass (T1-T0, T2-T0, T2-T1)
  - Changes in blood pressure (T1-T0, T2-T0, T2-T1)
  - Changes in smoking habit (T2-T0)
- MACE: the occurrence of events (cardiovascular (CV) mortality, all-cause mortality, near sudden cardiac death, ACS, CV intervention/surgery, CV hospital admission, CV emergency visits) as composite endpoint (T2-T0) are registered and collected by monthly telephone calls.
- General health:
  - Difference in depression score assessed by: PHQ-9 questionnaire (T1-T0, T2-T0, T2-T1)
  - Difference in anxiety score assessed by GAD-7 questionnaire (T1-T0, T2-T0, T2-T1)
  - Quality of Life: SF-36v2, difference in Physical Component Summary Score and Mental Component Summary Score (T1-T0, T2-T0, T2-T1)
  - Difference in dietary pattern (reflected by total score and score on individual components) assessed by Mediterranean Diet Score (T1-T0, T2-T0, T2-T1)
- Care utilisation as composite endpoint of: (number of) admissions, emergency visits and cardiac interventions (PCI, CABG) (T2-T0).
- Costs of care utilisation based on activities (clinical admission days, emergency and outpatient clinic visits, GP visits for cardiac (related) complaints or issues, radiology/cardiophysiology/nuclear and laboratory tests,

and cardiac interventions) registered at T0, T1 and T2 and collected by monthly telephone calls with the participants between T1 and T2.

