### 7.5 Randomisation, blinding and treatment allocation

At the start of the CR programme, once patients have indicated not to be interested in the regular CR programme, patients will be informed about the study and requested to participate. After receiving written consent from the patient they will be randomised in 1:1 ratio to the intervention group with mobile telemonitoring guidance or the control group with no mobile telemonitoring guidance or other CR programme by means of computerised allocation system applying an algorithm that prevents the care providers or the investigators from predicting the outcome of the randomisation

process. This means that the person, who determines if the patient is eligible, at the time of this decision, is unaware of which group the patient will be allocated to. The patient, care provider and outcome assessor will not be blinded to the intervention itself because of safety concerns.

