**Information Collection MACE, Care Consumption**

The occurrence of events (MACE (21) [cardiovascular mortality, all-cause mortality, near sudden cardiac death, acute coronary syndrome, CV Intervention/surgery, CV hospital admission, CV emergency visits]) and utilisation of care ((days) admission, outpatient clinic visits, GP visits, interventions, cardiophysiology, radiology, nuclear and lab testing) will be collected by a monthly telephone call with the participants using a standardised schedule throughout the study period. The telephone calls will be performed by a nurse. No advices or support will be given to the participants regarding their daily exercise or lifestyle changes.

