### **7.9 Follow-up of subjects withdrawn from treatment**

Patients in the study who experience a reintervention and get a new indication for CR will still be tested at 6 months and 12 months according to the original schedule. However, patients participating in the intervention group perceive no mobile telemonitoring guidance anymore. All patients will also be followed on major outcomes; relapse of myocardial infarction, death, PCI and CABG and utilisation of care.

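### SAP section 11 puts regular cardiac rehabilitation started during follow-up in neither cost term, so the cost difference and the ICER are biased if its uptake differs between arms

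*Combined protocol and SAP*

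**What the plan says.** SAP section 11 (Study objective 7, Health care cost estimation) has two cost terms. The first is "Costs for telemonitoring guidance (= CCR, only intervention group"). The second is "Sum of costs for medical services used outside CR (care utilization, = CCU"). The text above the accompanying table says: "Direct costs for mobile cardiac rehabilitation will be assigned for the intervention group (with telemonitoring guidance), but not for the control group (no intervention"). The table itself enters Yes for the cost of CR under mobile CR and No under control.

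The services to be priced are listed in three places:

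- SAP section 11: "clinical admission days, emergency and outpatient clinic visits, GP visits for cardiac (related) complaints or issues", followed by diagnostic and laboratory tests and cardiac interventions.
- Protocol 7.2.1: "Costs of care utilisation based on activities (clinical admission days, emergency and outpatient clinic visits", continuing with the same kinds of item.
- Protocol 7.6, for the monthly calls: "utilisation of care ((days) admission, outpatient clinic visits, GP visits, interventions, cardiophysiology, radiology, nuclear and lab testing").

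None of the three names CR sessions.

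Protocol 7.5 describes the comparator as "the control group with no mobile telemonitoring guidance or other CR programme". Protocol 7.9 deals with later events: "Patients in the study who experience a reintervention and get a new indication for CR will still be tested" at 6 and 12 months. For those in the mCR arm, telemonitoring then ends. Protocol 9.5 and SAP 4.2.1 analyse everyone as randomised. The ICER in SAP section 11 divides the difference in total cost by the difference in outcome, chiefly change in peak VO2 and the two SF-36v2 summary scores.

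**The concern.** The costing rule follows the treatment allocated, while the outcomes follow whatever treatment was received. A patient in either arm who has a reintervention, is newly indicated for CR and attends a regular course is costed at zero for that course. Any gain from it still counts in that patient's VO2peak and SF-36v2 scores. The ICER would then set an outcome difference that includes regular CR against a cost difference that leaves it out.

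At stake are the seventh hypothesis (lower cost of care use in the mCR arm) and the cost-effectiveness ratio. Protocol section 2 and SAP 1.3 both undertake to count costs saved as well as costs caused by mCR, and to compare mCR with other CR programmes. A regular course avoided in the mCR arm would be such a saving, and this rule cannot show it. The primary test of VO2peak is not affected.

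**Working it through.** The documents state no unit price, total cost, reintervention rate, CR uptake or ICER, so there is no figure of the plan's own to reproduce. The size has to come from algebra and labelled assumptions.

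**Notation.** M is the mean telemonitoring cost in the mCR arm. U_m and U_c are the mean costs of other care. C is the price of one regular CR course, taken as equal in the two arms. p_m and p_c are the shares of each arm that use one.

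**Cost difference, mCR minus control**

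- SAP rule: M + U_m - U_c
- CR costed as received: M + U_m - U_c + C x (p_m - p_c)
- Error (rule minus as received): C x (p_c - p_m)

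Each arm's own mean cost is understated by C x p_m or C x p_c. This holds whenever any patient uses regular CR, whether or not the two shares are equal.

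**Error in the ICER.** Divide by the outcome difference. For illustration I use the 3.0 ml/kg/min at 6 months from the sample size section (protocol 5.4, SAP section 3). The uptakes below are assumptions.

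| mCR uptake | Control uptake | Error in cost difference | Error in ICER, per ml/kg/min |
|---|---|---|---|
| 5% | 5% | 0 | 0 |
| 10% | 10% | 0 | 0 |
| 5% | 10% | +0.05 C | +0.017 C |
| 10% | 5% | -0.05 C | -0.017 C |
| 0% | 20% | +0.20 C | +0.067 C |
| 20% | 0% | -0.20 C | -0.067 C |

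A plus sign means that mCR looks too costly; a minus sign means that it looks too cheap.

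**In money**, assuming EUR 1,000 to 3,000 per course and a gap of 5 to 20 points in either direction:

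- Smallest: 1,000 x 0.05 = EUR 50 per patient, or 50 / 3.0 = about EUR 17 per ml/kg/min.
- Largest: 3,000 x 0.20 = EUR 600 per patient, or 600 / 3.0 = EUR 200 per ml/kg/min.

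With 119 patients per arm, a gap of 5 points is about 6 patients (0.05 x 119 = 5.95) and a gap of 20 points about 24 (0.20 x 119 = 23.8).

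**Relative to the mCR price.** If C is 0.5 to 3 times M, a 5-point gap shifts the cost difference by 0.05 x 0.5 = 2.5% to 0.05 x 3 = 15% of M.

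**Chance imbalance.** If true uptake is p in both arms, the observed gap has mean zero and SD sqrt(2p(1-p)/n). At n = 119 this is 1.8 points for p = 2% and 5.2 points for p = 20%. At n = 83, the planned number per arm after withdrawal, it is 2.2 and 6.2 points. This part is noise in the cost difference, not bias.

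**The case against.** The strongest reply is that the omission is symmetrical. Regular CR is left out of both arms, so the difference is unbiased when uptake is equal. A reader might infer from the Yes/No table that bias is certain, and the documents do not support that. Protocol 7.9 is a contingency rule with no rate attached, an indication is not attendance, and every participant declined regular CR at entry. This part of the reply stands. Equal uptake is, however, an assumption too. The fourth hypothesis expects fewer MACE with mCR, and MACE includes cardiovascular interventions, so fewer new CR indications in that arm would follow. The loss of telemonitoring after a new indication could push uptake the other way.

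A second reply is that CR in SAP section 11 means the study's mobile programme, so that regular CR could be entered as outpatient visits. That reading is strained. The table row is headed as the cost of CR in general, with mobile CR as one of its columns, and no list of services names CR sessions.

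Third, it cannot be said that CR sessions go unrecorded. The eCRF, the call schedule and the separate SAP definitions document are not available here. SAP 13.2 lists attendance at multidisciplinary sessions and reasons for leaving the CR programme among its T1 variables, though as predictors of adherence and not as priced services.

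Two further inferences would go too far. Protocol 7.5 and 7.9 do not conflict: the first describes the condition as allocated, the second what happens after a later event. And the VO2peak contrast stays interpretable, because a comparison by randomised group remains valid when some patients later receive other care. Knowing CR uptake by arm would help to explain that contrast but is not a condition for reading it.

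**Conclusion.** The point holds in conditional form. As SAP section 11 is most naturally read, regular CR started during follow-up is unpriced in both arms. Per-patient totals are then too low for anyone who uses it, and each arm's mean is too low by C x p. The cost difference and the ICER numerator are biased by C x (p_c - p_m) only if uptake differs by arm, and the documents fix neither the sign nor the size. The range of EUR 50 to 600 per patient, in either direction, rests wholly on assumed prices and uptakes. Whether that is material cannot be judged without an mCR price. The separate definitions document could alter the reading if it expressly assigns regular CR to a cost term. The matter should be settled before the cost analysis, because the stated rule gives wrong totals in cases that the protocol itself provides for.

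**What to change.** In SAP section 11, define CCR as the cost of any CR actually received, mobile or regular, assigned per patient in both arms. Change the control cell from No to as received. Make sure that the type of programme and the number of sessions are recorded at T1 and T2 and in the monthly calls. Report CR uptake by arm beside the cost results and the primary result. If the sponsor prefers to leave regular CR out, the SAP should say so, give the reason, and add a sensitivity analysis that includes it.

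The cost is a change of SAP wording, at most one eCRF item, one unit price and one table. The sections differ on when the monthly calls run: protocol 7.6 has them for the whole study, whereas protocol 7.2.1, the footnote to Appendix I and SAP section 11 place them between T1 and T2. If the latter applies, CR use in the first six months will depend partly on recall at T1.

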#### 4.7 Missing data

All collected data will be used in the data analysis, also data from the patient who discontinue the study until the time of study discontinuation. Missing data will be reported overall and by intervention and centre. We will describe patterns in missing data. We will analyse whether missing data are systematically different between both groups (*mCR* and control group) or whether they are related to baseline values or values on earlier time points. In case that the occurrence of missing values is systematically different between groups, or is related to other variables, multiple imputation methods will be used to calculate parameter estimates for sensitivity analysis.

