### 5.1 Efficacy analysis of primary study endpoint

The primary efficacy analysis will compare the change in peak oxygen uptake ( $VO_{2peak}$ /kg) from baseline (T0) to the 6 months follow up (T1) between the intervention and control group in the full analysis set.

$VO_{2peak}$ /kg will be derived from CPET. Approximated  $VO_{2peak}$  will be calculated from 6MWT as described under the definitions (document "EU-CaRE & EU-CaRE RCT SAP definitions").

The primary endpoint is the change in  $VO_{2peak}$  level between baseline (T0) and at 6 months (T1). It will be tested whether this change is different in the *mCR* and the control group by means of linear mixed models with the intervention as a fixed effect. The effect of centre on the outcome is modelled with a random effect. In the analyses we will adjust for the baseline value of  $VO_{2peak}$ . The null hypothesis is that there is no difference in mean change in  $VO_{2peak}$  level between the randomised groups. The alternative hypothesis is that the mean change in  $VO_{2peak}$  level differs between the randomised groups.

A covariance structure will be selected from several plausible structures. The covariance matrix resulting in the lowest Bayesian information criterion (BIC) fit statistic will be chosen.

To assess, if the underlying assumptions behind the mixed-effects model analysis are fulfilled, we will investigate normal quantile plots of residuals, standardized residuals, and random effects.

The linear mixed-effects model approach handles missing data appropriately and therefore multiple imputation or other methods to handle missing data in regard to the primary outcome will not be used. If necessary, the outcome variable will be transformed to obtain a normal distribution.

[figure not shown]

In case the groups differ on baseline values or other possibly confounding variables, the difference in change in  $VO_{2peak}$  level between baseline and 6 months between the intervention groups will be tested by means of linear mixed models analysis with centre as a random effect in which we will control for relevant confounders by adding covariates to the model. We will conclude a statistical significant difference in change in  $VO_{2peak}$  level between the *mCR* and control group when the two-sided p-value of the test statistic after adjustment for confounders is less than 0.05.

All analyses of PP will be in parallel to the description of the above.

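### SAP 11 lets per-patient costs be transformed to normality with no return to mean cost, and gives no rule for cost totals that cover less than 12 months

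*Combined protocol and SAP*

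**What the plan says.** SAP 11 builds one cost figure per patient: "A price will be assigned to each service and summed up for each patient individually". It defines total cost (TC) as the telemonitoring cost (CCR, mCR arm only) plus the cost of care used outside the programme (CCU, both arms). On testing it says: "Linear mixed models with centre as random effect will test differences between intervention and control group regarding total costs of care utilisation", and adds a pointer to section 5.1. Section 11 itself does not mention transformation, but section 5.1 does: "If necessary, the outcome variable will be transformed to obtain a normal distribution".

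SAP 10 (care use) specifies "linear mixed models with centre as random effect for continuous outcome or mixed models for logistic regression for dichotomous outcomes", and adds: "When necessary continuous outcome variables will be transformed to obtain a normal distribution".

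The ICER in SAP 11 divides the arm difference in total costs by the arm difference in outcome (change in peak VO2, and the SF-36v2 physical and mental component scores). It "will be estimated and a 95% confidence interval will be calculated"; no method is named.

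On incomplete follow-up, SAP 4.7 uses all collected data, "also data from the patient who discontinue the study until the time of study discontinuation". Protocol 7.9, on patients withdrawn from treatment, says: "All patients will also be followed on major outcomes; relapse of myocardial infarction, death, PCI and CABG and utilisation of care". Protocol 7.10 provides similar follow-up, including utilisation of care, for the patients it describes as leaving the study early.

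**The concern.** A payer or hospital needs the difference in arithmetic mean cost, because only the mean multiplied by the number of patients gives the budget. The ICER numerator is on that scale. A model on log cost compares geometric means, and the two comparisons can point in opposite directions. The arms also differ by construction: every mCR patient carries a programme cost that no control carries. A constant added to one arm lifts the smallest totals proportionally most, and those are the totals to which a log scale gives most weight.

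The second issue is follow-up. A sum over a shorter period is smaller. SAP 5.1 relies on the mixed model to handle missing data, but with a single total per patient there are no repeated values to draw on, so a partial total is either understated or dropped. The plan expects 30% withdrawal.

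At stake are the sixth and seventh hypotheses (lower care use and lower cost under mCR) and the cost-effectiveness objective. The primary VO2peak result is not affected.

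**Working it through.** **Inputs from the documents.** 83 patients per arm after withdrawal (SAP 3; the plan's own step reproduces, since 83/0.70 = 118.6, rounded up to 119). Withdrawal 30%. VO2peak difference 3.0 ml/kg/min, SDs 5 and 6. Two-sided alpha 0.05. The documents give no cost mean, SD, skewness or unit price, so every cost distribution below is an assumption. They do not name a log transformation either; it is taken as the usual choice for skewed costs. Centre effects are left out.

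**Step 1. Log-scale test with a fixed programme cost in one arm.** Control cost is lognormal with mean 1000. mCR cost is a fixed amount F plus a lognormal with mean 1000 − F, so the arithmetic means are equal and a valid test of means should reject in about 5% of trials.

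| Log-SD | F = 500 | F = 200 | F = 100 |
|---|---|---|---|
| 1.5 | 99.9% | 87% | 47% |
| 1.0 | 89% | 37% | 14% |

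A Welch test on untransformed costs rejects in 3.5% to 9.1% across these settings. At F = 500 and log-SD 1.5 the geometric mean ratio is about 2.5 against mCR although mean costs are equal. If mCR is truly cheaper (300 fixed plus a mean of 500 makes 800, against 1000; log-SD 1.5), the log test declares mCR significantly dearer in 89% of trials, while the ICER numerator would favour mCR.

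**Step 2. No fixed cost in the tested variable (CCU only).** With the same cost distribution in both arms (log-SD 1.5) the log test rejects in 4.8%. This rests on equal spread. With equal means but log-SDs of 1.0 and 1.2 it rejects in 24%, and with 1.0 and 1.5 in 88%, against 5.1% and 8.5% for the Welch test.

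**Step 3. Totals cut at dropout.** Assume a constant cost rate, dropout times spread evenly over 12 months, and no data after dropout. The share of 12-month cost captured at dropout proportion d is 1 − d/2.
- 30% in both arms: 0.85/0.85 = 1.00, no bias in the ratio.
- mCR 40%, control 20%: 0.80/0.90 = 0.89, an apparent 11% saving with no true difference.
- mCR 20%, control 40%: 0.90/0.80 = 1.125, an apparent excess.

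**Step 4. ICER denominator.** For VO2peak, SE = √(25/83 + 36/83) = √(61/83) = 0.857. At the planned difference, 3.0/0.857 = 3.5 and P(denominator ≤ 0) = 0.0002. At a true difference of 1.0 it is 0.12, and at 0.5 it is 0.28. With an assumed SE of 1,500 for the cost difference, and true effects from 0.5 to 3.0, a delta-method 95% interval covers in 72% to 99% of cases, while Fieller's covers in 95%. The SF-36v2 denominators cannot be assessed because no effect or SD is given.

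**The case against.** A reader might infer that the planned test does not compare mean cost at all. The documents do not support that. Untransformed, the model in SAP 11 estimates a centre-adjusted difference in arithmetic mean cost. Transformation is conditional and reaches costs only by cross-reference. This stands, but the condition is departure from normality, which summed admissions, visits and interventions are likely to show.

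It can also be said that the large rejection rates need the programme cost to be in the tested variable. The hypothesis concerns costs of care utilisation, which could mean CCU alone. This stands too: the wording fits either TC or CCU. When the fixed cost is in, the errors in Step 1 run against mCR, so they would not create a false saving.

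Three further stronger readings fail. Costs are not shown to be full of zeros, since protocol 6.1 gives both groups standard outpatient cardiology care and SAP 11 prices outpatient visits. No text says that costs are summed only to discontinuation: SAP 4.7 is a general rule, and protocol 7.9 and 7.10 continue to follow care use. Nor does the SAP prescribe a naive interval for the ICER. It names no method, so a bootstrap or Fieller interval would comply. Finally, dichotomous care-use outcomes go to logistic mixed models, so not all care use is in linear models.

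**Conclusion.** The point holds as a gap in specification with a real consequence if the stated rule is followed. The SAP permits a transformation of costs and of continuous care use without a route back to mean cost, and a test run that way can disagree with its own ICER. Under assumed lognormal costs with equal means and equal log-SDs, false rejection is about 5% if the fixed telemonitoring cost is excluded. It is 37% to 99.9% if that cost is 20% to 50% of the mean, and lower for a smaller fixed cost (14% at one tenth of the mean with log-SD 1.0). Unequal spread alone can also produce it.

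The follow-up issue is an unresolved difference between SAP 4.7 and protocol 7.9 and 7.10. The size of any bias depends on dropout figures that the documents do not give by arm, and there is none in the ratio if dropout is equal and alike in timing under the assumptions of Step 3. The unnamed ICER method alone is missing detail; at the planned VO2peak effect the denominator is well away from zero. The change is worth making because it is cheap and bears on a stated objective.

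**What to change.** 1. In SAP 11, remove the transformation option for costs. Estimate the untransformed difference in mean 12-month cost, with a bootstrap interval resampled within arm and centre.
2. State whether TC or CCU is tested.
3. In SAP 10, analyse care-use counts with a negative binomial model, with log follow-up time as offset and centre in the model.
4. Reconcile SAP 4.7 with protocol 7.9 and 7.10 so that care data collected after withdrawal are used, and state what is done with totals that still fall short of 12 months.
5. Take the ICER interval from the same bootstrap, or use Fieller's method, and show the replicates on the cost-effect plane. Adding net benefit or an acceptability curve is a choice of presentation.

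The cost is SAP wording and a little more programming, with a possibly wider interval for the cost difference. No new data are needed.
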